### Cost-effectiveness analysis

The average costs and effects of tubal flushing during HSG with oil-based contrast and water-based contrast during fertility work-up will be compared. Total costs of the HSG, fertility treatments and fertility outcomes (collected using the eCRF) will be evaluated after a follow-up of six months after randomization. These data will be used to calculate the direct medical costs.

Societal costs will be measured using digital iPCQ questionnaires after six months of follow-up [24]. Cost categories that will be included are: (1) healthcare costs (primary and secondary care, complementary care and home care); (2) lost productivity costs (absenteeism from paid and unpaid work, and presentism) and (3) patient costs (informal care and other care services paid for by patients themselves).

Valuation for participants from the Netherlands and the United Kingdom will be according to their respective national guidelines [25, 26]. For the valuation of health care utilization, lost productivity and informal care, standard costs for the Netherlands and the United Kingdom will be used. Medication use will be valued using prices of the Royal Dutch Society for Pharmacy (www.KNMP.nl) and the NICE British National Formulary (www.bnf.nice.org.uk). Patient and family costs other than informal care will be valued using self-reported prices. For the valuation of absenteeism from paid work, the friction cost approach will be used.

### Safety monitoring

The IRB determined that the study related risk for participants is very low. A Data Safety Monitoring Committee was therefore not deemed necessary. An interim analysis is not planned. All adverse events (AEs) occurring within one month after HSG will be reported to the IRB by line listing yearly. Additionally, adverse neonatal outcomes such as a congenital anomaly or birth defect will be reported as severe adverse events (SAEs). SAEs occurring within one month after HSG will be reported to the IRB immediately through the Dutch national web portal ToetsingOnline. SAEs occurring in participants outside of the Netherlands will additionally be processed according to local regulations. All SAEs will be followed until they have abated, until a stable situation has been reached or the patient was discharged.

### Data management and monitoring

Patient information will be filled in anonymously based on randomization number. Linking personal data to the study number can only be performed in the local participating centres. Written informed consent forms are stored in the local participating centre, all forms and data will be archived for 25 years in the participating centres according to GCP and local regulations. Monitoring of study processes will be done according to national and international guidelines by an independent study monitor [27]. Annual safety reports will be sent to the accredited IRB and the competent authority.

See Additional file 1: Table S1 for the completed WHO Trial Registration Data Set [28].

## Discussion

Increasing female age is one of the main causes of infertility in the twenty-first century, with > 50% of the women undergoing IVF being over 35 years of age [29, 30]. Anovulation and tubal pathology are also important causes of infertility. As a consequence, the results of this H2Oil2 study are estimated to be applicable to more than 50% of infertile women seen in fertility clinics.

This multicentre randomized controlled trial will generate insight in the potential fertility enhancing effect of tubal flushing using oil-based contrast during HSG in infertile women who are 39 years or older, women with ovulatory disease, and women with a high risk for tubal pathology. The generated evidence can guide clinicians and policy makers to decide which subgroups of women will benefit from an HSG with oil-based contrast as a therapeutic intervention, whether the intervention is cost-effective and if the risk of adverse events is acceptable.

### Strengths and limitations

The proposed study is specifically designed to detect a difference in ongoing pregnancies leading to live births for three important subgroups of infertile women. Most randomized clinical trials regarding the fertility enhancing effect of oil-based contrast during HSG have been previously performed in couples with unexplained infertility and/or mild male factor. While several trials have also included women with other types of infertility [31–34], none were able to show a significant positive effect of tubal flushing with oil-based contrast mostly due to a low sample size, and the results of previous trials among women with unexplained infertility cannot simply be extrapolated to all women facing infertility [14]. Another strength of this study is its multinational character. As it involves academic and non-academic (teaching and non-teaching) participating centres from the Netherlands and the United Kingdom, the results will be applicable to different countries with different hospital settings. A limitation of this study is the potential diversity in treatments between the various participating centres. The participating centres will treat patients according to their local protocol. Although these protocols are based on national guidelines, there is variety between the national guidelines of the participating countries [4, 35]. As this study evaluates two variants of standard care which are already applied in current practice, we chose this pragmatic approach to generate evidence that is applicable to the majority of the treating centres. This approach will lead to a difference in management between participating centres, possibly influencing the chance of conception. Randomization is therefore stratified per inclusion group and per inclusion site, to prevent uneven distribution among the two randomization groups.

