### Participants

Women who are scheduled for an HSG as part of their fertility work-up can participate if they meet at least one of the following criteria: (1) women who are 39 years of age or older, (2) women who have an ovulation disorder (ovulation disorders will be defined as less than eight menstrual cycles per year), or (3) have a high risk for tubal pathology (high risk will be defined as a past chlamydia infection, pelvic inflammatory disease, peritonitis, known endometriosis and/or pelvic surgery including tubectomy for ectopic pregnancy). In order to ensure adequate sample sizes in all three groups of participants, women meeting more than one criterion will be included according to the criterion that comes first in ranking. The ranking is based on the expected prevalence of the three subgroups of women within the study population, with the lowest expected prevalence highest in ranking. Women will be excluded if they have an endocrine disorder known to decrease natural pregnancy chances (e.g. diabetes, unregulated hypothyroidism or hyperthyroidism), iodine contrast medium allergy or a male partner with severe infertility (a pre-washed total motile sperm count below three million sperm per millilitre).

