### Sample size

Our hypothesis is that HSG with oil-based contrast will increase the live birth rate with 10% in three infertility groups: (1) women aged 39 years or older, (2) women with ovulation disorders and (3) women who have a high risk for tubal pathology. To detect an increase of 10% in live birth rate from 17 to 27%, 395 women per group are needed (alpha 1%, beta 20%, Z-test with unpooled variances as calculated in PASS 2020). Anticipating a loss to follow-up rate of 15%, the total number of participants required is 930 (465 in each arm of the trial). With this number we have 80% power to study the 10% difference in live birth rate in the intervention versus control group in the stratified design using Cochrane-Mantel-Haenzel.

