### Statistical analysis

Categorical data will be reported as absolute numbers and percentages. Normally distributed continuous variables will be summarized as means with standard deviations, and non-normally distributed continuous variables will be reported as medians with interquartile ranges. The primary analyses will done according to the intention to treat (ITT) principle, including all randomised women. Differences in live births will be expressed as crude and stratification adjusted risk ratio and absolute risk difference with associated 95% and 99% confidence intervals (CI) using log-linear binomial regression. We will construct Kaplan–Meier curves, estimating the cumulative probability of conception leading to live birth over time and use the log-rank test to assess differences. Additionally, we will do a cox proportional hazard analysis to evaluate the difference in primary outcomes over time while accounting for the subgroups and evaluating presence of interaction. Continuous outcomes will be measured at multiple time-points and will be analysed with the use of linear mixed models. We will subsequently compare intervention and control treatment within the stratified groups (1) women aged 39 years or older, (2) women with ovulation disorders and (3) women who have a high risk for tubal pathology. Women meeting more than one criterion will be included in the group that comes first in ranking as described earlier. Within these stratified groups pregnancy outcomes will be expressed as risk ratio, risk difference and hazard ratio with 95% CI.

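### The 80% power belongs to the pooled oil-versus-water comparison only, yet the article presents the trial as sized to detect the difference for three subgroups and to show which of them benefit

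*Protocol article*

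**What the plan says.** The Sample size section of the protocol article sizes a single two-arm comparison: "To detect an increase of 10% in live birth rate from 17 to 27%, 395 women per group are needed", with "alpha 1%, beta 20%, Z-test with unpooled variances as calculated in PASS 2020". After allowing for 15% loss, the total is 930. The power statement that follows is for the overall contrast, stratified by a Cochran-Mantel-Haenszel analysis: "With this number we have 80% power to study the 10% difference in live birth rate in the intervention versus control group".

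Other sections speak of the three diagnosis groups (age 39 or older, ovulation disorder, high risk for tubal pathology) as if the design served each of them:

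- Participants introduces the ranking rule for women who meet several criteria with the words "In order to ensure adequate sample sizes in all three groups of participants".
- Outcomes hypothesises higher pregnancy rates and a shorter time to pregnancy in all three subgroups.
- Discussion says that the evidence can help clinicians and policy makers "decide which subgroups of women will benefit from an HSG with oil-based contrast as a therapeutic intervention".
- Strengths and limitations lists as a strength: "The proposed study is specifically designed to detect a difference in ongoing pregnancies leading to live births for three important subgroups of infertile women".

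For the analysis, Statistical analysis says: "Within these stratified groups pregnancy outcomes will be expressed as risk ratio, risk difference and hazard ratio with 95% CI". It also plans a Cox model that accounts for the subgroups and evaluates interaction.

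**The concern.** The article claims a capability for the subgroups, but its only power calculation is for the combined population. It gives no size, power or significance level for a comparison within a subgroup.

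The likely harm is misreading. Suppose oil-based contrast raises live birth by 10 points in all three groups. Three separate comparisons, each with about even odds of reaching significance, will most likely look like a treatment that works in some groups and not in others. A reader who has been told that the trial was designed to detect the difference in these groups would take a non-significant group as evidence of no benefit. That could lead to a real benefit being withheld from women in that group.

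**Working it through.** **Inputs.** From Sample size: 17% versus 27%, alpha 1%, power 80%, unpooled Z-test, 395 evaluable per arm, 15% loss, 465 per arm randomised. From Randomization and blinding: 1:1 allocation, stratified by diagnosis. From Statistical analysis: 95% intervals within subgroups, so effectively 5% two-sided. Not in the article, and therefore assumed: each subgroup's share of the women, and that 17% versus 27% holds within a subgroup.

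**1. Reproduce the plan's figure.** The variance sum is 0.17 × 0.83 + 0.27 × 0.73 = 0.1411 + 0.1971 = 0.3382.

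n per arm = (2.576 + 0.842)² × 0.3382 / 0.10² = 394.98, so 395. Then 395 / 0.85 = 464.7, so 465 per arm and 930 in total.

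Both figures match. The alpha must be two-sided, because a one-sided 1% test gives 340 per arm. This is the size of one comparison over all women.

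**2. Power within a subgroup.** Power = Φ(0.10 / √(0.3382 / n) − z), with n evaluable women per arm in the subgroup, and z = 1.960 at 5% or 2.576 at 1%.

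| Share of the women | n per arm | Power at 5% | Power at 1% |
|---|---|---|---|
| 20% | 79 | 33% | 15% |
| 25% | 99 | 40% | 19% |
| one third | 132 | 51% | 27% |
| 50% | 198 | 68% | 44% |

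For one third, n = 131.7 and the standard error is √(0.3382 / 131.7) = 0.0507. Then 0.10 / 0.0507 = 1.973, which gives Φ(0.013) = 50.5% at 5% and Φ(−0.603) = 27.3% at 1%.

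**3. A bound that needs no assumption about the split.** The smallest of three groups cannot hold more than a third of the women. Its power is therefore at most about 51% at 5% and 27% at 1%. With no loss at all (465 / 3 = 155 per arm) the ceiling is 57% and 33%.

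**4. What 80% in one subgroup would need.** At 5%: (1.960 + 0.842)² × 0.3382 / 0.10² = 265.4, so 266 evaluable per arm. That is 266 / 395 = 67% of the trial, or 266 / 465 = 57% with no loss. Either share is more than half, so at most one subgroup could have it. At 1%, a subgroup would need 395 per arm, which is the whole evaluable trial. For all three subgroups at 5%, the need is 3 × 2 × 266 = 1,596 evaluable women.

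**5. How a uniform effect would look.** Take equal thirds, a 10-point effect in every group and power 0.505 in each:

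- All three reach 5%: 0.505³ = 0.129.
- None does: 0.495³ = 0.121.
- One or two do: 1 − 0.129 − 0.121 = 0.75.

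**The case against.** The best defence is that the article does not contradict itself. The sentence under Strengths and limitations does not say that the difference will be detected in each subgroup. What follows it contrasts this population with the unexplained-infertility populations of earlier trials, so it can be read as naming who is studied. Sample size openly assigns the power to the overall comparison. Both observations are right, and they limit the point to how the design is described. They do not remove it: Participants speaks of adequate numbers in all three groups, and a statement about which subgroups benefit has no meaning for a pooled estimate.

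The ranking rule also does more than bookkeeping, because it moves women with overlapping criteria into the rarer group and so enlarges it. But the rule as described sets no minimum. Even a quota, if the full protocol has one, could not lift the smallest group above a third of 930.

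Some stronger readings are tempting and are not supported:

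- *Every subgroup has 51% / 27% power.* That needs equal thirds. The ranking by expected prevalence suggests unequal groups, so some would have less and some more.
- *The sample size is wrong.* It reproduces exactly for its purpose.
- *Interaction is ignored.* The Cox model already evaluates it, and further detail may lie in an analysis plan that is not shown.
- *The subgroup analysis carries a 14.3% false-positive risk against 1%.* The figure 1 − 0.95³ counts both directions and assumes that each interval is used as a test. The article sets no such rule. False benefit in at least one group would be 1 − 0.975³ = 7.3%, against 0.5% for the pooled test.
- *Subgroup intervals should be 99%.* Using 95% for secondary estimates is ordinary practice. Judged by 99% intervals, a one-third subgroup's power would fall from 51% to 27%.

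**Conclusion.** The point holds as a mismatch between the stated design claim and the design. The 80% power at two-sided 1% applies to the pooled, stratified comparison and to nothing narrower. The claims in Participants, Discussion and Strengths and limitations go beyond it.

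For the smallest subgroup, power is at most about 51% at 5% and 27% at 1%, and it is lower if the groups are unequal. This rests on 17% versus 27% within that subgroup and 15% loss, but not on any assumed split. A subgroup with a lower control rate would have more power for the same 10-point difference and less for the same risk ratio. The 75% chance of a mixed picture additionally assumes equal thirds and the same effect in all groups.

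The primary outcome, alpha, sample size and primary analysis are unaffected. What changes is what may be concluded about individual subgroups.

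**What to change.** 1. In Participants, Discussion and Strengths and limitations, say that the design and its 80% power apply to the combined population. In Participants, describe the ranking rule as enlarging the rarer groups, not as ensuring adequate numbers.
2. Describe the within-subgroup comparisons as exploratory. Give their power as a range under stated assumptions about subgroup share and event rates, not as a single figure.
3. Base any claim that benefit differs between subgroups on a treatment-by-diagnosis interaction for the binary primary outcome, not on whether separate 95% intervals exclude no effect. Name one scale in advance (risk ratio or risk difference), because a non-zero effect that is constant on one scale is not constant on the other when control rates differ between groups. Acknowledge that this test too will have limited power.

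Sample size can stay as it is, and the 95% subgroup intervals can stay. The cost is some rewording and one model term, with no extra women. The downside for the sponsor is a less favourable subgroup claim.

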### Potential impact and implications

As health care costs are increasing around the world, research focusing on cost-effectiveness of healthcare will help clinicians and policy makers to determine the appropriate position of the HSG with oil-based contrast within the fertility workup, taking into account both its diagnostic potential as well as its therapeutic effect. A cost-effectiveness analysis of the long term outcomes of the H2Oil study showed an increase in the cumulative pregnancy rate when oil-based contrast was used, compared to when water-based contrast was used (80,0 versus 75,0%) [36]. The higher price of the oil-based contrast was compensated by a decrease in the need for ART to achieve these pregnancies in the group receiving oil-based contrast, resulting in comparable overall costs. The study concluded that tubal flushing with oil-based contrast was therefore cost-effective in comparison to water-based contrast in women with unexplained subfertility [36]. In the proposed study, a cost-effectiveness analysis will be performed incorporating medical consumption, absence from (paid) work and loss of productivity due to health problems [24].

The mechanism of action of oil-based contrast leading to a fertility enhancing effect is not fully elucidated. Different hypotheses place the point of action in the Fallopian tube [37, 38], the endometrium [39], and the peritoneum [40, 41]. A post-hoc analysis of the H2Oil-study showed that in the group of women with higher pain scores, the ongoing pregnancy rate was higher in women that had received oil-based contrast during HSG when compared to women that had received water-based contrast [42]. These result support the first hypothesis that when using oil-based contrast medium, the pain was caused by an increase in intrauterine pressure prior to dislodgment of pregnancy-hindering debris from the proximal part of otherwise anatomically normal Fallopian tubes [42]. Previous research associated pre-procedural anxiety to a higher experienced pain level during medical procedures [19, 43]. To further investigate the relationship between discomfort or pain during HSG and ongoing pregnancies in the current study, the APAIS questionnaire will be used to score pre-procedural anxiety as a confounder for experienced pain.

Despite reassuring recent research on the prevalence of complications after an HSG, fear of complications is still a reason for some clinicians to withhold use of oil-based contrast [11, 18]. A recent review, without publication date or language restrictions, showed that the incidence of intravasation of contrast in the venous or lymphatic system is higher during tubal flushing with oil-based contrast in comparison to water-based contrast (2.8% and 1.8% respectively, odds ratio 5.05, 95% CI 2.27 to 11.22) in the included RCTs [18]. However, when including only studies that used fluoroscopy screening during HSG, no serious consequences of intravasation were identified. Pelvic infection after HSG is another well-known complication, the previously mentioned review described that in studies published in or after 1960, as antibiotics were not routinely used before, the frequency of infection was 0.55% after HSG with oil-based contrast and 0.35% after HSG with water-based contrast [18]. The proposed study aims to provide information on the complication rate in a population of women that have a higher risk for tubal pathology (because of a previous infection, pelvic surgery or endometriosis). Complications will be reported systematically.

This multicentre RCT will establish whether, for women that are 39 years or older, women with ovulation disorders, and women who have a high risk for tubal pathology, there is a fertility enhancing effect of tubal flushing at HSG with oil-based contrast during fertility work-up and if this is cost-effective.

## Abbreviations

AE: Adverse event
APAIS: Amsterdam Preoperative Anxiety and Information Scale
ART: Assisted Reproductive Technology
CI: Confidence interval
HSG: Hysterosalpingography
iPCQ: IMTA Productivity Cost Questionnaire
IRB: Institutional Review Board
ITT: Intention to treat
IUI: Intra uterine insemination
IVF: In vitro fertilization
NICE: National Institute for Healthcare and Excellence
PCOS: Polycystic ovary syndrome
RR: Relative risk
SAE: Severe adverse event
VAS: Visual Analogue Scale
